### Statistics analyses

Microsoft Access 2010^®^ will be used as a database of information on included patients. Data from the questionnaires are scanned via ReadSoft Forms© (ReadSoft AB, Helsingborg, Sweden) into another database. Before data analyses the two databases will be merged.

The data analyses will comprise four main procedures:

1. Longitudinal analyses by multivariate linear mixed effect regression model, in which changes over a period of 2, 4 and 8 weeks will be compared. This will include analysis of a) whether there is a significant difference in the intervention and control group during the follow-up, and b) if the changes are similar for the two groups in between the measurements at respectively 2, 4 and 8 - week follow-up. In order to determine whether there is a difference in survival between the two groups Kaplan-Meier plot is used. Survival in the two groups is also compared in a Cox regression, which can be controlled for the same variables as the analyses of questionnaire data.

2. Intention to treat analyses, in which changes in outcome variables between the intervention and control group of caregivers, will be tested by linear “mixed-effect” regression models for repeated measurements. These analyses will be conducted for outcomes both before and after the patient’s death. To investigate the possible effect modifications, relevant interactions will be included, among these interactions between the randomization group and time since baseline, time since diagnosis, and baseline values of outcomes.

3. Data collected in semi-structured interviews after the intervention will be analyzed qualitatively to identify how a selection of the bereaved caregivers have experienced the care of the patient in their homes and how they have experienced the intervention.

4. Cost-effectiveness analyses, in which multivariate regression models will be used to analyze differences in costs between the intervention- and control-group, and to relate these to observed differences in effects.

5. Data collected in 10 – 12 focus groups will be analyzed to describe the experiences of the professionals involved in the trial; their evaluation of cooperation and quality of treatment and care in the patient trajectories.

### Trial plan

The trial is completed when the 340 patients have been randomized and after the last patient has been followed six months from baseline. Data collection is estimated to go on for 2 years. However, the caregivers will continue to be followed 19 months after the death of the patients.

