## Background

The Capital Region of Denmark had in 2013 1,735,521 inhabitants with one of the highest incidences (0.6%) and prevalence (4.3%) of cancer in the world as well as a high cancer mortality rate (6.8%). Almost five thousand of the inhabitants of the Capital Region dies of cancer every year (0.25%) [1]. Thus, a substantial need for palliative cancer care is observed.

Studies have shown that most patients with advanced cancer prefer to spend the last part of their life at home (50-90%) [2,3]. However, in most western countries more than half of the patients with advanced cancer die in hospitals [3-9]. A recent systematic review by Gomes *et al.* showed that most people with different terminal diseases preferred to die at home and the majority of patients did not change preferences as their illnesses progressed [10]. Similar preferences were reported in a retrospective Danish survey, which indicated that the majority of cancer patients in the palliative care phase preferred to die in their own home (81%); however, the reported preference for dying at home decreased towards time of death (64%) [11]. Further, a recent prospective Danish study indicated that the majority (71%) of cancer patients in palliative care preferred to die in their own home [12]. According to the National Board of Health, 55% of Danish cancer patients died in hospitals, 18% in nursing homes or in specialist palliative care institutions, while only 26% died at home in 2005 [13]. A similar pattern is seen in other European countries, as the place of death in Europe is most frequently hospital or nursing home [14]. Even in the UK, which has a well-developed and comprehensive national palliative care system, a study analyzing all cancer deaths between 1993 and 2010 showed that 48% died in a hospital and 16% in hospices, while 25% died at home [15]. Timely and continuous involvement of General Practitioners (GP), nurses and - when necessary - a Specialized Palliative Care Team (SPT) seems to have a positive impact on the likelihood of dying at home [16,17]. Experience from the UK also showed that pronounced delay in the discharge from the hospital was a major obstacle to achieving the preferred place of palliative care and death [18].

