### Study objectives

The primary aim of DOMUS is to investigate whether an accelerated transition process from oncological treatment to SPC at home for patients with incurable cancer results in prolonged residence in their preferred place of care, which indirectly may increase the number of home deaths. The secondary aims are to investigate whether the intervention:

– relieves patients’ symptoms (pain, tiredness, drowsiness, nausea, vomiting, dyspnea, insomnia, appetite, constipation, and diarrhea)

– improves patients’ and the closest relatives’ quality of life (health related quality of life)

– relieves patients’ as well as caregivers’ psychosocial problems (depression, anxiety, dyadic coping, and caregiver burden)

– ameliorates the bereavement process among the closest relatives (anxiety, depression, loss- and restoration-oriented coping, prolonged grief, sleep, lifestyle)

– prolongs survival of patients

improves cooperation between professionals

– is cost-effective

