				2, 7, 13, 19 months
	• Prolonged Grief Disorder (PG – 13) [46]			7, 13, 19 months
	• Lifestyle single items			Week 2
				2, 7, 13, 19 months
Blood samples	• Telomere length		Baseline	2 months
Databases^c^	• Number of hospital admissions	From Baseline to 6 months	From Baseline to 6 months	
	• Number of inpatient bed days			
	• Number of outpatient visits to hospitals			
	• Number of visits to GP			
	• Number of visits to the emergency room			
	• Number of visits to the emergency physician			
	• Number of visits to specialists			
	• Treatments in public hospitals			
	• Prescribed drugs			
	• Place of care and death			
Healthcare services	• Health insurance charges	From Baseline to 6 months	From Baseline to 6 months	
	• Pharmacy prices			

^a)^The bereaved is the primary caregiver, ^b)^Only patients with participating relatives, ^c)^The National Patient Register, Health Insurance Registry, Medicine Databases.

In addition, patient’s informal caregivers are asked for a blood sample.

Databases will be used to collect data about the patients and caregivers use of healthcare (Table 2). All planned assessments, questionnaires, and medical records are shown in Table 2.

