### Statistical methods

#### **
*Sample size estimations*
**

Sample size was calculated considering the primary purpose of this trial, which is to prolong patients’ residence at home and to increase the number of patients who die at home by 15 - 20%. The latter purpose serves as a proxy for the first purpose. With a power of at least 80%, and an effect difference of 15% at a significance level of 0.05, 170 patients are required in each study arm (Ficher´s exact test). On the basis of this and an expected dropout rate of 10-15%, we plan to randomize 380 patients for the study.

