
Another issue of discussion in the DOMUS trial has been to define the inclusion criteria. Cancer patients who are eligible for SPT can be defined in many ways depending on the purpose of the study or clinical outcomes. A RCT by Temel *et al.* demonstrated that patients with newly diagnosed metastatic lung cancer benefitted from referral to a SPT, as these patients achieved better quality of life, were less depressed and lived longer than patients in a control group who received standard therapy [48]. Thus, the Temel study was engaged in early intervention of SPC for a specific cancer diagnosis [48], whereas our study is engaged in defining patients with different cancer diagnoses treated at a comprehensive cancer center in need of SPC at home. Therefore, in addition to the expressed wish (and agreement between patient and closest relative) to be cared for at home, we have selected the inclusion criteria “incurable cancer with limited or no antineoplastic treatment left” (List of Inclusion and exclusion criteria of the DOMUS study). Further, we have characterized the meaning of “incurable cancer with limited or no antineoplastic treatment left” for all involved diagnoses (Table 1). Hence, we have sought to define a palliative patient population suitable for and in need of SPC at home, which of course can be adapted to other diagnoses as well. By defining limited treatment options, we have established a set of criteria that are already an integrated part of oncological treatment. With these criteria, we may in the future enable clinicians to proactively identify patients in the oncological treatment trajectory, who may benefit from SPC. In the initial phase of the inclusion of patients ECOG performance status 2–4 was an inclusion criterion. However, after a year of inclusion only 66 patients were enrolled. In order to speed up recruitment of patients as well as attempting to study earlier SPC [29,48] we have decided to remove the criteria (ECOG performance status 2–4). Further, by deleting the inclusion criteria it will be possible to investigate the difference effect of SPC in low and high ECOG performance status patients. The changes will be reported to clinicaltrial.gov.

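### Table 2 gives place of death a register window of baseline to 6 months, yet home death sizes the trial and nothing beyond an undefined dropout allowance covers patients still alive then

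*Protocol article*

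**What the plan says.** - **Sizing outcome.** Under Sample size estimations, the purposes are longer residence at home and "to increase the number of patients who die at home by 15 - 20" per cent, the second standing as proxy for the first. The inputs are "With a power of at least 80" per cent and "an effect difference of 15% at a significance level of 0.05". They lead to 170 per arm by Fisher's exact test, and to 380 randomised after a 10-15% dropout that is not defined. No control rate is given.
- **Collection window.** Under Assessments, Table 2 lists "Place of care and death" among the register items. The window for that block is baseline to 6 months. It stands once, at the head of the block, and I read it as covering every row.
- **End of trial.** Under Trial plan: "The trial is completed when the 340 patients have been randomized and after the last patient has been followed six months from baseline". Only caregivers are expressly followed longer, to 19 months after the patient's death.
- **Eligibility change.** In the Discussion: "we have decided to remove the criteria (ECOG performance status 2–4"). The reasons are slow recruitment (66 patients in a year) and an interest in earlier palliative care. No new size or window is described.
- **Survival.** One secondary aim in Study objectives is whether the intervention "prolongs survival of patients".

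**The concern.** Place of death exists only for patients who have died. With a 6-month window, anyone alive at month 6 has no value on the outcome that sizes the trial. Two denominators are then open.

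- **Deaths only.** The analysis loses patients. It also conditions on an event after randomisation that the trial hopes to delay, so the groups compared are no longer those that were randomised.
- **All randomised**, with home death by 6 months as the event. This keeps the randomised comparison. But the 15-point difference shrinks in proportion to 6-month mortality, and a patient who lives past month 6 counts the same as one who died in hospital.

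Dropping the performance-status restriction admits fitter patients, so more should be alive at month 6. An analysis plan can choose between the denominators, but it cannot recover places of death that were never extracted. What is at stake is whether the trial can answer the question it was sized for.

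**Working it through.** **Inputs.** Two-sided alpha 0.05 (sidedness is not stated; assumed). Difference 15 points. Control home-death rate p = 0.26, the national figure in Background ("while only 26% died at home in 2005"); using it here is an assumption. The share dead by 6 months, f, is not in the article and is shown as a range.

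**Step 1: the plan's own figure.** With 0.26 against 0.41 the mean is 0.335, and

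n = [1.960·√(2·0.335·0.665) + 0.842·√(0.26·0.74 + 0.41·0.59)]² / 0.15² = (1.308 + 0.555)² / 0.0225 ≈ 154.2, so 155 per arm.

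The continuity correction, (n/4)·[1 + √(1 + 4/(0.15·n))]², gives 168. Exact Fisher power at 170 per arm is 80.9%. The stated 170 is therefore reproduced at a 26% control rate.

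**Step 2: the dropout allowance.** 340/0.90 = 378 and 340/0.85 = 400. The planned 380 covers 1 − 340/380 = 10.5% loss from all causes.

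**Step 3: deaths only.** Evaluable patients per arm are 170·f with 340 randomised and 190·f with 380. Exact two-sided Fisher power, 26% against 41%:

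| Dead by 6 months | 340: n per arm | Power | 380, no other loss: n per arm | Power |
|---|---|---|---|---|
| 90% | 153 | 76.1% | 171 | 81.2% |
| 80% | 136 | 70.5% | 152 | 76.0% |
| 70% | 119 | 64.1% | 133 | 69.5% |
| 50% | 85 | 48.2% | 95 | 53.8% |

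If 380 are randomised and 10% also drop out, the four powers are 76.5%, 71.0%, 64.7% and 48.9%.

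**Step 4: all 340 in the denominator.** The rates become f·0.26 and f·0.41, with 170 per arm:

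| Dead by 6 months | Rates compared | Power |
|---|---|---|
| 90% | 23.4% v 36.9% | 74.4% |
| 80% | 20.8% v 32.8% | 66.8% |
| 70% | 18.2% v 28.7% | 58.2% |
| 50% | 13.0% v 20.5% | 40.4% |

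**Step 5: if survival differs (illustration only).** Suppose 70% of controls and 60% of intervention patients die by 6 months.

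- No effect on place of death: 0.70·0.26 = 18.2% against 0.60·0.26 = 15.6%, an apparent deficit.
- True 15-point benefit among deaths: 18.2% against 0.60·0.41 = 24.6%, power 25.6%. With equal 70% mortality it would be 58.2%.

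**Step 6: sensitivity to the control rate.** At 42.5% against 57.5%, Fisher power at 170 per arm is 75.0% before any survivor is counted. The deaths-only figures with 340 randomised are then 69.9%, 64.1%, 57.5% and 45.5%. Part of that shortfall comes from the control rate and not from the window.

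**The case against.** The strongest reply is that the Trial plan sets a closing date tied to the last patient, not a limit for each patient. Recruitment is given as June 2013 to June 2015, so the first patients could be observed for about 30 months. Under uniform accrual and exponential survival, 50-80% mortality at 6 months becomes about 83-97% dead at closing. Deaths-only power (26% against 41%) is then about 73-80% with 340 and 78-84% with 380. This stands as a description of what is possible. But the article does not say that place of death is collected up to closing, and the one window it gives is 6 months. Following caregivers after bereavement would reveal some later deaths, only for patients with a participating caregiver, and no extended collection of place of death is stated.

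Several stronger readings are tempting and are not supported:

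- A reader might infer that the size calculation counts every randomised patient as having a place of death. It does not: it inflates 340 to 380. With 380, 10% survivors and no other loss, power is still 81%.
- A reader might infer that either denominator gives a wrong answer. Home death by 6 months among all randomised is a valid randomised comparison. It answers a different, diluted question, and it works against the intervention only if survival is prolonged, which is hoped for and not established.
- A reader might infer that the survival comparison also stops at 6 months. Statistics analyses states no such limit.
- A reader might infer that the size was never reconsidered after the ECOG change. The article is silent, which is not the same.

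It is also fair that home death is called a proxy for time at home, and that the handling of survivors can belong in an analysis plan. Neither point supplies the missing data.

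**Conclusion.** The point holds for the data-collection window and the sizing. Taken as written, Table 2 leaves patients alive at 6 months without the outcome on which the trial is sized, and only an undefined 10-15% dropout is available to absorb them. At 340 randomised and 26% against 41%, power falls below 80% in every scenario shown: from 80.9% to between 76% (10% alive) and 48% (50% alive) among deaths, or between 74% and 40% with all randomised as denominator. At 380 the deaths-only range is 81% to 54% if nothing else is lost.

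The direction of the loss is secure; its size is not, because the article gives neither 6-month mortality nor a control rate for the calculation. Bias from differential survival is conditional on a survival effect. If place of death is in fact extracted up to the closing date, the loss is smaller, and the article should say so.

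**What to change.** In Table 2 and the Trial plan, state that place and date of death are taken from the registers beyond 6 months for every randomised patient, until death or to one common late cut-off by which nearly all have died. Make the home-death comparison at that point.

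If the 6-month window is kept, say how patients alive at month 6 count and restate power for the expected 6-month mortality. To have 340 known places of death would need 340/f randomised: 378, 425, 486 or 680 for f = 0.9, 0.8, 0.7 or 0.5, before any dropout.

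Days alive and at home in the first 180 days, among all randomised, would be a useful supporting measure that needs no conditioning on death. It is optional and not a required replacement.

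The cost is a longer register extract and a later read-out of home death, with no added patient contact. Separately, 340 (Abstract, Study design, Trial plan) and 380 (Sample size estimations) must be reconciled, since the margin for survivors depends on which applies.

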### Ethics

The National Committee on Health Research Ethics, Denmark (37237) and The Danish Data Protection Agency (2007-58-0015) have approved the DOMUS trial.

The DOMUS trial has the logical consequence that the two groups of patients do not receive the same care. This can be justified mainly by the lack of evidence of whether accelerated transition from oncological treatment to SPC at home as a whole has any effect on place of care and death, symptoms/problems, quality of life, survival and caregivers’ health and grief. Further, it should be emphasized that the patients in the control group will receive the same treatment and care as they previously had, and as others in similar circumstances. As already mentioned the control group has the possibility of being referred to the same treatment and care as the intervention group with the exception of the psychological intervention. However, the GPs can refer patients in the control group to psychological treatment outside of the trial. Finally, the study staff will not prevent a potential crossover of patients.

## Discussion

The DOMUS trial is a comprehensive RCT in incurable cancer patients – to our knowledge the first of its kind - including outcomes from the individual patient and closest relative, as well as healthcare research of economy and organization. The primary goal of this trial is to ensure accelerated transition from hospital to SPC at home, so patients with incurable cancer can obtain timely transferal to and prolonged residence in their own homes [11]. The model is based on already existing resources, which are organized in a fixed sequence – a “fast-track lane” - with the addition of a manualized psychological intervention. The psychological intervention aims to support patients and caregivers jointly, as coping with severe illnesses depends, not only on the individual, but the dyad [47]. The effect of accelerated transition to a SPT enriched with a psychologist intervention will hopefully provide further knowledge of the needs of patients and caregivers as well as the costs and the expenses associated with the intervention. Finally, our study will, due to the transparency (Ref: Clinicaltrials.gov Identifier: NCT01885637) and the present paucity of comprehensive RCTs regarding clinical, organizational and health economical aspects of SPC, be valuable for decision-making in our region as well as in countries with comparable healthcare systems, and hopefully also be a source of inspiration for other healthcare systems [31,48]. In developing the DOMUS trial, the authors have discussed several issues, which may raise criticism and pose challenges to feasibility and influence outcomes. One of them is obtaining agreement between patients and relatives about place of care. In our population, we have no data on the degree of agreement, which of course may be highly dependent on the quality and extent of information. In the DOMUS trial, this information is given by trained research nurses and based on an information manual regarding SPC at home. In a retrospective study, 80% of the patients and relatives agreed on the preferred place of death, and 20% of the relatives changed their minds (in 51% of these cases the preference moved from home to another setting) [49]. However, in this study the patients’ preferred place of death was given by the relatives after the deaths of their loved ones, and therefore the “true” proportion of agreement is uncertain [49]. Based on the retrospective data and our clinical experience, we anticipate that thorough and proper information about SPC at home will create agreement in the majority of cases.

Another issue of discussion in the DOMUS trial has been to define the inclusion criteria. Cancer patients who are eligible for SPT can be defined in many ways depending on the purpose of the study or clinical outcomes. A RCT by Temel *et al.* demonstrated that patients with newly diagnosed metastatic lung cancer benefitted from referral to a SPT, as these patients achieved better quality of life, were less depressed and lived longer than patients in a control group who received standard therapy [48]. Thus, the Temel study was engaged in early intervention of SPC for a specific cancer diagnosis [48], whereas our study is engaged in defining patients with different cancer diagnoses treated at a comprehensive cancer center in need of SPC at home. Therefore, in addition to the expressed wish (and agreement between patient and closest relative) to be cared for at home, we have selected the inclusion criteria “incurable cancer with limited or no antineoplastic treatment left” (List of Inclusion and exclusion criteria of the DOMUS study). Further, we have characterized the meaning of “incurable cancer with limited or no antineoplastic treatment left” for all involved diagnoses (Table 1). Hence, we have sought to define a palliative patient population suitable for and in need of SPC at home, which of course can be adapted to other diagnoses as well. By defining limited treatment options, we have established a set of criteria that are already an integrated part of oncological treatment. With these criteria, we may in the future enable clinicians to proactively identify patients in the oncological treatment trajectory, who may benefit from SPC. In the initial phase of the inclusion of patients ECOG performance status 2–4 was an inclusion criterion. However, after a year of inclusion only 66 patients were enrolled. In order to speed up recruitment of patients as well as attempting to study earlier SPC [29,48] we have decided to remove the criteria (ECOG performance status 2–4). Further, by deleting the inclusion criteria it will be possible to investigate the difference effect of SPC in low and high ECOG performance status patients. The changes will be reported to clinicaltrial.gov.

The planned intervention is complex, including several sequential elements, and therefore it will not be possible to evaluate single elements of this multimodal trajectory intervention. The accelerated transition from oncological treatment requires a flexible primary care setting and a SPT ready to take care of the patient at home within five days of enrolment in the trial. The SPTs in the Capital Region of Denmark have their own individual referral guidelines and operate in less well-defined local areas. To ensure an equal distribution of patients to the different SPTs, the DOMUS protocol allocates patients to relevant SPTs according to uniformed referral guidelines and geographical based allocation. The geographical distribution of adequate SPC and the collaboration between SPTs, GPs, and district nurses is a rather simple prerequisite for the delivery of good palliative care. In addition, this issue may play a significant role even in countries with well-developed palliative care. In the UK with a comprehensive coverage of palliative care obtainable across the country, there seems to remain a lot of inequity, including that relating to geography, diagnosis, age and ethnicity [50]. In the DOMUS trial we will, in addition to the introduction of uniformed referral guidelines and geographical based allocation, further investigate these issues by adding qualitative interviews with patients, informal caregivers and healthcare professionals.

Currently a psychological intervention is not included in the standard SPT in Denmark, although it is recommended that a SPT consist of doctors, nurses, and one or more other medical professionals [14,51]. In five out of nine SPTs in the Capital Region a psychologist is already part of the hospice/palliative care unit team, but as the capacity is limited the psychologists are only used for in-patients except in two palliative care units, where they can participate in SPC at home [32]. However, as all SPTs of the region have agreed to participate in the DOMUS trial, the standardized manualized psychologist intervention is applied to all patients and relatives allocated to the intervention group. Thus, if the multimodal trajectory intervention enriched with a targeted psychologist intervention proves to be successful it may inspire the future model for SPC.

The intervention proposed in the DOMUS trial requires a consistent and intensified collaboration between healthcare professionals in the hospital, the primary healthcare sector and the SPTs in order to give the patients the best possible care at home. The DOMUS study is primarily important, because it can show whether the intervention can improve the treatment of palliative patients and provide a model for how the SPC should be organized in the community. It is essential to find out whether place of care and death, longer survival and healthcare benefits are associated with the intervention. As the organizational and financial consequences of the model will also be investigated, there is a direct basis on which decisions can be taken regarding the organization of future palliative care. In addition to national importance of the study it has great international relevance, since high quality evidence from RCTs is sparse in palliative care, and no RCTs with an accelerated transition from oncological treatment to continuing SPC at home in patients with incurable cancer have previously been published.
